#### Premature termination or withdrawal of subjects

If premature study termination occurs, all available data will be published. In accordance with section 10, subsection 4, of the Medical Research Involving Human Subjects Act, the sponsor will suspend the study if continuation is deemed to jeopardise participant health or safety. The accredited Medical Ethics Committee (METC) will be notified without undue delay, and the study will remain suspended until a positive decision is obtained. Participants will be informed accordingly. Participants may withdraw at any time without consequences. The investigator may also withdraw participants for urgent medical reasons. To maintain the target sample size, an additional participant will be recruited if withdrawal occurs during the run-in period. If withdrawal is unrelated to the study (eg, relocation), a new participant will be recruited. Withdrawn participants will be followed up via online questionnaires, with assessments conducted via telephone if needed.

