### Sample size calculation

This feasibility pilot study evaluates an intervention protocol not previously studied. A sample size of 18 patients was deemed sufficient to assess the primary objective, based on consultation with a statistician.^39 40^ The sample size calculation considers a significance level of alpha=0.05, power of 0.8, estimated feasibility of 0.9, and a lower bound of 0.7 for study exclusion. This sample size minimises patient exposure while providing enough data to inform the future RCT.

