### Outcomes

#### Primary outcome

##### Feasibility

Attrition rate, defined as the percentage of participants completing the study protocol. The intervention will be considered feasible if ≥70% of participants complete the study while attending ≥75% of acupuncture sessions.

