### Statistical analysis

Continuous data will be presented as mean±SD if normally distributed and as median with IQR otherwise. Categorical data will be presented as proportions. The 95% CI will be calculated for all primary and secondary parameters, with significance set at α=0.05. The primary outcome, attrition rate, is defined as the proportion of participants completing the study. Attendance at 100%, ≥75% and ≥50% of acupuncture sessions will be reported. Feasibility is confirmed if ≥70% of participants complete the study while attending ≥75% of sessions, informing a future RCT design. Secondary feasibility outcomes include consent rate, satisfaction and personnel capacity. Consent rate is the proportion of approached participants who provided consent, with age distribution reported as mean±SD or median (IQR). Reasons for non-participation will be described. Satisfaction scores (5-point Likert scale) at weeks 6, 10 and 14 will be summarised, visualised with bar plots and analysed descriptively. Personnel requirements will be summarised.

A table will summarise acupuncture points. Safety analysis includes AE frequency. Efficacy, assessed as the proportion no longer meeting Rome IV criteria, will be analysed using McNemar’s test. Due to the study design, no efficacy claims can be made without a control group.

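### Children who leave for reasons called unrelated are replaced, but the article does not say they stay in the denominator of a primary endpoint that measures completion

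*Protocol article*

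**What the plan says.** The Primary outcome section, under Feasibility, gives the endpoint: "Attrition rate, defined as the percentage of participants completing the study protocol". The label says attrition, but the quantity defined is completion. The decision rule follows: "The intervention will be considered feasible if ≥70% of participants complete the study while attending ≥75% of acupuncture sessions". The Statistical analysis section repeats the definition: "The primary outcome, attrition rate, is defined as the proportion of participants completing the study". Neither section says which children form the denominator if some have been replaced.

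The section on premature termination or withdrawal has two replacement rules. One concerns the run-in: "To maintain the target sample size, an additional participant will be recruited if withdrawal occurs during the run-in period". The other stands alone and carries no time limit: "If withdrawal is unrelated to the study (eg, relocation), a new participant will be recruited". Relocation is the only example given; the article offers no further definition and does not say who decides. The same section says that withdrawn children are followed up by online questionnaire, or by telephone if needed.

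Under Visit 1, children who meet the modified Rome IV criteria over the run-in are then enrolled to receive acupuncture. Under Visit 2, eligibility is confirmed from the diary, a bowel clean-out of two to three days follows, and the first session takes place once that has succeeded.

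On size, "A sample size of 18 patients was deemed sufficient to assess the primary objective", from "a significance level of alpha=0.05, power of 0.8", "estimated feasibility of 0.9, and a lower bound of 0.7 for study exclusion".

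**The concern.** In most trials a replacement makes up for an outcome that was lost. Here nothing is lost. A child who leaves in week 5 has a fully observed primary result, which is non-completion. If a new child takes that place and the first is no longer counted, a failure has been removed from the endpoint. The error goes in one direction only.

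The rule is also open to judgement. Whether a withdrawal was unrelated is decided after it has happened, in an open-label single-arm study, with no stated definition beyond the example. The same completion figure feeds the interim look after 10 children, where the principal investigator makes the final decision on continuation.

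What is at stake is the go/no-go for the randomised trial that is meant to use this intervention protocol. That trial will also lose children who move away or leave for neutral reasons, so the rate it needs for planning is completion counted against all causes of loss.

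**Working it through.** **Inputs from the article.** N = 18; alpha 0.05 (sidedness not stated); power 0.80; expected feasibility 0.90; lower bound 0.70; pass rule of at least 70% completing with at least 75% of sessions attended. Below, completion means meeting both parts of that rule.

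**Input not in the article.** The rate of unrelated withdrawal among enrolled children, u. I assume 2%, 5% and 10%.

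**The plan's own figure.** With the variance taken at the expected value and two-sided alpha:

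n = (1.960 + 0.842)² × 0.9 × 0.1 / (0.9 − 0.7)² = 7.849 × 0.09 / 0.04 = 17.66, rounded up to 18.

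The sample size reproduces.

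**Pass mark.** 12/18 = 66.7% fails and 13/18 = 72.2% passes, so 13 completers are needed.

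**Putting replaced children back.** With x completers among 18 counted children and k replaced children restored, the rate is x/(18 + k). The table gives the smallest k that takes the rate below 70%.

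| Counted result | Rate | Smallest k that reverses it | Rate with those children restored |
|---|---|---|---|
| 13/18 | 72.2% | 1 | 13/19 = 68.4% |
| 14/18 | 77.8% | 3 | 14/21 = 66.7% |
| 15/18 | 83.3% | 4 | 15/22 = 68.2% |
| 16/18 | 88.9% | 5 | 16/23 = 69.6% |

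**Chance of passing.** Let c be true completion among all enrolled children, and u the fraction of enrolled children who withdraw, are called unrelated and leave the denominator. The apparent rate is c/(1 − u). The chance of passing is the exact binomial probability of 13 or more out of 18 at that rate.

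| True c | u | Apparent rate | P(at least 13/18) |
|---|---|---|---|
| 65% | 0 | 65.0% | 35.5% |
| 65% | 2% | 0.65/0.98 = 66.3% | 40.0% |
| 65% | 5% | 0.65/0.95 = 68.4% | 47.6% |
| 65% | 10% | 0.65/0.90 = 72.2% | 61.8% |
| 60% | 0 | 60.0% | 20.9% |
| 60% | 2% | 0.60/0.98 = 61.2% | 24.1% |
| 60% | 5% | 0.60/0.95 = 63.2% | 29.6% |
| 60% | 10% | 0.60/0.90 = 66.7% | 41.2% |
| 90% | 0 | 90.0% | 99.4% |
| 90% | 2% | 0.90/0.98 = 91.8% | 99.8% |

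For scale, u = 10% is 1.8 of 18 children. It makes 0.10/0.35 = 29% of non-completers unrelated when c = 65%, and 0.10/0.40 = 25% when c = 60%. With u = 2% those shares are 6% and 5%.

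**If replaced children stay in.** With a denominator of 18 + k the rate estimates c itself and there is no bias. The whole effect depends on the sentence the article does not contain.

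**The case against.** The strongest reply is that the replacement sentence is a recruitment rule. The endpoint is defined over participants, and the article still calls those who leave participants and follows them up. Recruiting a substitute while keeping the withdrawn child in the denominator is compatible with every sentence, and analysis sets may be laid down in a full protocol or analysis plan that is not shown. This stands in part. A reader might infer that the plan computes completion without the replaced children; the article does not say so, and I do not claim it. What remains is that a stated rule, read in the ordinary sense of replacement, conflicts with a stated endpoint, and nothing in the article rules that reading out.

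A reader might also extend the criticism to the run-in. The text does not support that. Enrolment to acupuncture follows the run-in, so replacing a run-in loss removes no enrolled non-completer. The stated purpose of holding the target sample size is also attached to the run-in sentence, not to the one on unrelated withdrawal.

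The size can be disputed too. Ten per cent is an assumption at the upper end of the range shown, the reversal by a single child occurs only at exactly 13/18, and at the planned 90% the pass is almost certain either way. All of that is correct. The rule matters when true completion is near or below the threshold, which is where a go/no-go criterion has to discriminate.

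Finally, a family that moves away says little about whether acupuncture is tolerable, so setting aside clearly external losses answers a legitimate question. It does, but as a supporting result with reasons fixed beforehand, because the later trial will suffer those losses as well.

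**Conclusion.** The point holds as an unresolved conflict between the replacement rule and the primary endpoint, with a known direction and an unknown size. If replaced children leave the denominator, the completion rate can only rise. Near the threshold this matters: one child reverses 13/18, and for u between 2% and 10% the chance of passing goes from 36% to between 40% and 62% at a true 65%, and from 21% to between 24% and 41% at a true 60%. At the planned 90% it is negligible.

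These figures rest on two assumptions: that replaced children are not counted, which is the usual meaning but is not stated, and that u lies in the assumed range, for which the article gives no figure. The conclusion that the denominator must be fixed in advance depends on neither. It follows from withdrawal being the outcome itself.

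**What to change.** Amend the withdrawal, primary-outcome and statistical analysis sections as follows.

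- Define the primary denominator as every child confirmed eligible and enrolled after the run-in at visit 2, including any lost during the clean-out before session 1. Starting the count at session 1 would leave those children out.
- Count withdrawal after that point, for any reason, as non-completion.
- Let a replacement add to the denominator; it does not substitute for the child who left.
- Report run-in withdrawals separately. Their replacement can stay as it is.
- List beforehand the reasons that count as clearly external, and report the rate without those children only as a sensitivity analysis.
- Use the same denominator rule at the interim look.

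The cost is a few sentences and no new data. The stated completion rate may be slightly less favourable.

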#### Data Safety Monitoring Board

Given the low-risk nature of the study, with only eight acupuncture sessions over 10 weeks and no expected serious adverse effects, a Data Safety Monitoring Board is not required.

### Outcomes

#### Primary outcome

##### Feasibility

Attrition rate, defined as the percentage of participants completing the study protocol. The intervention will be considered feasible if ≥70% of participants complete the study while attending ≥75% of acupuncture sessions.

### Secondary outcomes

#### Feasibility

Consent rate, patient and parent satisfaction (measured at weeks 6, 10 and 14 via a 5-point Likert scale), and assessment of required personnel capacity for a future RCT (measured at end of study via open feedback by involved staff members on feasibility and workload).

#### Acupuncture points

Documentation of targeted acupuncture points.

#### Safety

Occurrence of AEs (needle-related pain, irritation, haematomas, headache, syncope, sedation, neuropathy) assessed at weeks 3, 6, 10 and 14. Severity and treatment relation will be recorded.

#### Efficacy

Treatment success, defined as resolution of FC per Rome IV criteria at the end of the intervention (EOI).^3 37^ Rome IV criteria will be assessed by the investigator at the screening visit (visit 1) and at the EOI visit. For the EOI assessment, the criteria will be assessed over the last 4 weeks of the acupuncture intervention, or, in the event a participant discontinues the study prematurely within 4 weeks, over the intervention period. Other efficacy endpoints will be assessed via symptom diaries, the endpoints, including quality of life and school absence, are based on a previously published core outcome set^45^:

Defecation frequency (bowel movements/week).Stool consistency (Bristol Stool Scale).Painful defecation (yes/no).Faecal incontinence frequency (episodes/week).Withholding behaviour (yes/no).Abdominal pain (yes/no, Visual Analogue Scale score).Spontaneous bowel movements (>24 hours after escape medication).Time between acupuncture and defecation.Bowel movements <24 hours after acupuncture.Escape medication use and effect.

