#### Visit 2: screening and first acupuncture treatment (t=0)

After the run-in period, eligibility is confirmed based on the diary information, according to the modified Rome IV criteria. A bowel clean-out regimen (bisacodyl or enemas) is initiated for 2–3 days (box 1). On successful bowel clean-out, the first acupuncture session begins.

Box 1Escape medication

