### Escape medication

As is common in paediatric research settings, if a child does not defecate for 72 hours or experiences faecal impaction symptoms, escape medication (bisacodyl or enemas) will be given daily for up to a maximum of 3 days.^37 41 42^ If ineffective, the participant will be examined and withdrawn if faecal impaction is present. Dosage regimens adhere to the European Society for Pediatric Gastroenterology Hepatology and Nutrition^10^ and the Dutch Pediatric Formulary (https://www.kinderformularium.nl/) recommendations (box 1). Patients requiring disimpaction eight or more times during the intervention are considered treatment failures and will be withdrawn.

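### A very early drop-out can be scored as a treatment success at an end of intervention the child never reached, and the eight-disimpaction failure label is not carried into that endpoint

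*Protocol article*

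**What the plan says.** All references are to the protocol article.

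- **Outcomes, Efficacy.** Treatment success is resolution of functional constipation by Rome IV at the end of the intervention. For that visit "the criteria will be assessed over the last 4 weeks of the acupuncture intervention". For early leavers the window changes: "in the event a participant discontinues the study prematurely within 4 weeks, over the intervention period".
- **Table 1, third footnote.** A child is a case at entry when at least two Rome IV criteria are met during the 2-week run-in.
- **Visit 2.** Eligibility is confirmed from the run-in diary. Then "A bowel clean-out regimen (bisacodyl or enemas) is initiated for 2–3 days", and "On successful bowel clean-out, the first acupuncture session begins".
- **Escape medication.** The trigger is "if a child does not defecate for 72 hours or experiences faecal impaction symptoms". The section then states: "Patients requiring disimpaction eight or more times during the intervention are considered treatment failures and will be withdrawn". A second route withdraws a child who is still impacted after escape medication has not worked; no failure label is attached to that route.
- **Statistical analysis.** Efficacy is the proportion of children who have stopped fulfilling Rome IV, tested with McNemar's test. Neither withdrawal nor the failure label is mentioned. The section also rules out efficacy claims because there is no control group.
- **Premature termination or withdrawal of subjects.** A child who withdraws during run-in, or for a reason unrelated to the study, is replaced.

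**The concern.** There are two separate defects.

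**The shortened window.** The endpoint is meant to describe status at the end of a 10-week course. For a child who leaves within 4 weeks, the stated rule describes the days after a bowel clean-out instead. The clean-out acts directly on one criterion, the large faecal mass in the rectum. In a very short window, criteria that depend on an event occurring (painful, hard or large stools, retention) also have fewer days in which to show. A case needs two criteria, so losing one can turn a child into a success. Both effects push the same way: leaving early makes a resolved score more likely.

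**The failure label.** The Escape medication section declares a failure; the endpoint definition does not take it up. On a literal reading, a child withdrawn after eight disimpactions who meets only one Rome IV criterion is a failure in one section and a success in the other.

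The success proportion is the first-named efficacy endpoint and the only one given a named test. The Introduction says the pilot should supply enough endpoint information to design a later randomised trial. An upward bias in this proportion would be passed on to that design.

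**Working it through.** **1. The plan's own figures.** The protocol gives no figure for treatment success. The denominator is the planned 18, which reproduces from the Sample size inputs (0.9 against 0.7, power 0.8, alpha 0.05 taken as two-sided, variance at 0.9):

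n = (1.960 + 0.842)² × 0.9 × 0.1 / (0.9 − 0.7)² = 17.66, rounded up to 18.

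**2. The windows side by side.**

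| Assessment | Length | Position relative to clean-out |
|---|---|---|
| Baseline | 2 weeks | before it |
| Child reaching week 10 | 4 weeks | starts about 6 weeks after it (10 − 4) |
| Child leaving within 4 weeks | under 4 weeks, no minimum | starts directly after it |

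The window is shorter than baseline only for exits before 2 weeks. The clean-out effect applies to every exit within 4 weeks and is strongest for the earliest.

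**3. Do the two defects concern the same children?** Under the 72-hour trigger, eight episodes take at least 8 × 3 = 24 days, against a 28-day limit for the shortened window. Impaction symptoms could trigger episodes sooner. The two groups are therefore largely different.

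**4. Size per child.** One child moved between success and non-success shifts the proportion by 1/18 = 5.6 points.

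**5. Ceiling.** Two counts of non-completers can be taken from the plan:
- at the expected 90% completion, 0.1 × 18 = 1.8, about 2 children: 2/18 = 11.1 points;
- at the limit of the feasibility rule, 13/18 = 72.2% passes and 12/18 = 66.7% does not, so at most 5 children: 5/18 = 27.8 points.

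At 90% completion the chance of at least one non-completer is 1 − 0.9¹⁸ = 85%. All of these count failure to complete the whole study, not exits before week 4.

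**6. Illustration.** The success rate among completers is not in the protocol. I assume 30%, 40% or 50%, rounded to whole children, with exact (Clopper–Pearson) 95% intervals shown for the 40% case.

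| Completers, drop-outs | Assumed rate | Drop-outs as non-success | Drop-outs all as success |
|---|---|---|---|
| 16, 2 | 30% | 5/18 = 27.8% | 7/18 = 38.9% |
| 16, 2 | 40% | 6/18 = 33.3% (13.3–59.0) | 8/18 = 44.4% (21.5–69.2) |
| 16, 2 | 50% | 8/18 = 44.4% | 10/18 = 55.6% |
| 13, 5 | 30% | 4/18 = 22.2% | 9/18 = 50.0% |
| 13, 5 | 40% | 5/18 = 27.8% (9.7–53.5) | 10/18 = 55.6% (30.8–78.5) |
| 13, 5 | 50% | 6/18 = 33.3% | 11/18 = 61.1% |

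**7. The test.** Every enrolled child meets Rome IV at baseline, so changes can go only one way. With b conversions the exact two-sided McNemar p is 2 × 0.5^b: 0.0625 for b = 5 and 0.031 for b = 6. One drop-out scored as a success can cross 0.05.

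**The case against.** Several counter-arguments have weight.

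- **The failure label.** A reader might infer that the plan codes withdrawn treatment failures as successes. It does not say so. The Escape medication section calls them failures, and the Efficacy section can be read as defining success for everyone else. How the label enters the dataset may be settled in an analysis plan that is not shown. What stands is that the two sections do not refer to each other.
- **The contradictory child.** A child with eight disimpactions is likely to meet more than one criterion: movements within 24 hours of a laxative, enema or suppository are not spontaneous, and impaction bears on the faecal-mass criterion. Meeting only one is possible but not shown.
- **The size.** A reader might take 11 to 28 points as the plan's own expected bias. The 10% and 30% describe non-completion of a study running to week 14, with attendance of at least 75% of sessions, and 30% is a tolerance limit. A child leaving in weeks 5–9 already has 4 weeks of treatment to assess, and one lost in follow-up has the ordinary window. This objection stands in full.
- **The window length.** Baseline itself used 2 weeks, and two criteria are weekly rates. This weakens the fewer-days argument for exits at 2–4 weeks, but not the clean-out argument.
- **The stakes.** The endpoint is secondary, and the protocol disclaims efficacy claims. That limits the severity.

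Scoring observed data by a pre-specified rule can be defended in general. It is harder to defend here, where the observed days follow a clean-out and the endpoint is named for a time the child did not reach.

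**Conclusion.** The point holds in limited form. The stated rule lets a child who leaves very early count as resolved at end of intervention, on a window with no minimum length that begins right after clean-out. The failure label is not carried into the endpoint or its analysis, so those sections must be reconciled.

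The effect is 5.6 points per child. The range of 11 to 28 points is an upper bound. It assumes 2 to 5 non-completers, that all of them leave early and that all are scored as successes, with 18 as denominator; the protocol supplies no rate for exits before week 4. The documents do not support treating the eight-disimpaction children as generally falling in the shortened window, given the 24-day minimum under the 72-hour trigger.

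This should be corrected before the efficacy data are analysed. It does not touch the primary feasibility outcome or the sample size.

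**What to change.** Add one sentence to the endpoint definition and repeat it under Statistical analysis. In the main analysis, a child is a success only if treatment continued to the end of intervention and Rome IV is not met over its last 4 weeks. Any child who discontinues treatment earlier, or is withdrawn by either route in the Escape medication section, counts as non-success.

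Keep the shortened-window scoring as a sensitivity analysis, and report how many children are classified differently.

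State how replaced children enter the denominator, separately for withdrawal in run-in and withdrawal unrelated to the study. Without this, it is unclear whether both the replaced child and the replacement count.

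The change is analytic only; no treatment, withdrawal or escape-medication rule is altered. The cost is a slightly conservative proportion, because a child who leaves improved counts as non-success. How far this affects departures such as relocation depends on the denominator rule, since those children are already replaced.
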